### Stage 3: Implementation of intervention

Stage 3 is the *implementation* phase and will begin with the training of an occupational therapist who will administer the manualized intervention. This individual will be trained by the Principal Investigator and/or Co-Principal Investigators. Any issues arising from this training will be identified and subsequent training will be modified accordingly. Given the additional mood component in this study, there is the potential for the identification of individuals with serious mental health concerns. As such, a psychologist (LW and/or a consulting Clinical Psychologist) will be available should the intervention of a mental health professional be required throughout the project. With respect to participants, we will recruit a sample of 20 individuals with MS who meet the inclusion criteria from the Ottawa Hospital MS Clinic. The sample size was selected so that we can ensure that we have 15 individuals in the final sample (allowing for 25% attrition). This number was chosen given that previous research has suggested a minimum sample size of 12 to 15 is sufficient to determine feasibility of pilot studies in MS (68, 69). The primary inclusion criteria is that participants exhibit evidence of objective CF on the PASAT as defined by established normative data using ≥1.5 standard deviations below the mean (36). Inclusion criteria also include: (a) English-speaking; (b) ages 18–65 years; (c) EDSS <6.0; (d) relapse and steroid free in the past 30 days; (e) purposeful exercise ≤2 days per week for 30 min; (f) asymptomatic (i.e., no signs or symptoms of acute or uncontrolled cardiovascular, metabolic, or renal disease) based on the Get Active Questionnaire (70), (g) sufficient visual function to complete cognitive tasks (e.g., no scotomas) and (h) access to an internet-enabled device to participate in the intervention. Exclusion criteria are: (a) other neurological, medical or psychiatric condition that might impede cognition (e.g., traumatic brain injury, learning disability) excluding depression and anxiety; (b) current dementia; (c) substance use or dependence disorder; (d) hearing impairment that would interfere with the ability to effectively take part in the videoconference sessions.

The research assistant will be available to perform participant screening on the inclusion criteria, the Get Active Questionnaire and the PASAT during all MS Clinics until the sample size is reached. For those meeting eligibility requirements, a baseline assessment session (lasting approximately 120 min) will take place at the Ottawa Hospital for each participant with outcome measures administered by a research assistant (see Table 3). These outcomes measures were chosen given the multidimensional nature of fatigue in MS, and given that these variables are, or have the potential to be, related to CF. The pre-intervention assessment will take place at least 1 week before the beginning of the intervention to ensure that participants can wear an accelerometer (to monitor physical activity) for at least 1 week to establish baseline physical activity. The 8-week, group-based intervention will involve weekly 70-min videoconference calls facilitated by the licensed occupational therapist (with sessions reviewed by the psychologist). Given the sample size, we anticipate three separate groups (i.e., no more than 7 per group). These three groups will be provided at different times of day to allow scheduling flexibility for participants. The facilitator will promote discussion within group members by calling on individual participants during the calls to allow for interaction, social learning and peer support. Homework will be a component of the program and will be reviewed at each subsequent session. Abbreviated make-up sessions will be offered on an as-needed basis for participants who need to miss a class. Completers will be defined as individuals who attend at least 6/8 sessions (i.e., 75%). After each session, the facilitator will complete SOAP notes (subjective, objective, assessment, plan) to document their impressions (71). Within 2 weeks of the last videoconference session, participants will return to the Ottawa Hospital for a follow-up assessment session (∼120 min) where outcome measures (using alternate forms where possible) will again be administered by a research assistant.

**Table 3 T3:** Outcome measures for the behavioural intervention.

Outcome	Measures
Cognitive fatigability	Paced Auditory Serial Addition Test (83), Psychomotor Vigilance Task (84), F-2-MS (78)
Subjective fatigue	Modified Fatigue Impact Scale (77), Fatigue Scale for Motor and Cognitive Functions (16), Fatigue Symptoms and Impacts Questionnaire-Relapsing MS (17)
Cognition	Brief International Cognitive Assessment for MS (Symbol Digit Modalities Test (85), learning trials of the California Verbal Learning Test-II (86) & Brief Visuospatial Memory Test-Revised) (87), Phonemic and semantic fluency (88)
Mood	Hospital Anxiety and Depression Scale (80), Patient Health Questionnaire-9 (89) Generalized Anxiety Disorder-7 (90) Depression Anxiety and Stress Scale (91)
Health-related quality of life	Multiple Sclerosis Quality of Life (MSQOL)-54 (92)
Sleep quality	Pittsburgh Sleep Quality Index (81)
Physical	Free-living activity using accelerometer (ActiGraph GT3X-BT; processed using ActiLife software) (www.actigraphcorp.com)
Self-efficacy	Likert scale (93) regarding confidence in ability to manage MS fatigue
Structured Interview	Structured interview with participants regarding knowledge and attitudes toward the intervention (quantitative based on Likert ratings) with items reflecting the seven component constructs of the Theoretical Framework of Acceptability (94)
Feasibility	Eligible participants excluded or not agreeing to participate; completion rate of assessments; attendance at intervention sessions; adherence to homework; attrition; facilitator SOAP notes

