### Stage 4: Analysis and dissemination

Stage 4 involves *analysis and dissemination of results*. Data will first be compiled and analyzed using IBM SPSS Statistics (version 28). Descriptive statistics will be compiled to characterize the sample. Comparisons between baseline and follow-up on the outcome measures for all completers will be conducted using *t*-tests. The primary outcome measure is feasibility and will be evaluated according to the following: eligible participants excluded or not agreeing to participate, completion rate of assessments, attendance at intervention sessions, adherence to homework, attrition, and facilitator SOAP notes. The secondary outcome measure is CF performance on the PASAT. CF scores will be derived according to previously documented procedures (36). The intervention will be considered effective if at least a small effect size (i.e., improvement in CF) is observed between baseline and follow-up. Data from the structured interview will be analyzed quantitatively. Facilitator SOAP notes will be subjected to thematic analysis. Knowledge translation will involve traditional dissemination routes (i.e., journals, conferences) with the additional plan to disseminate this research among health care professionals by providing in-service presentations and hospital rounds. We will also seek to disseminate the findings to the lay public through community presentations, and educational materials. It is our intention to include trainees at all levels in this research to educate new health care professionals on the benefits of behavioural interventions on patient outcomes. We will also engage a Patient Advisory Committee to seek input on other possible avenues of communicating the results from this study to individuals in the MS community. We will follow CONSORT reporting guidelines for pilot feasibility trials (72).

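### Stage 4 calls the intervention effective on any small uncontrolled pre-post gain in the PASAT fatigability score used to select participants; the rule cannot support that conclusion, and the baseline score is not identified

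*Protocol article*

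**What the plan says.** **Selection.** In Stage 3 the primary inclusion criterion is that "participants exhibit evidence of objective CF on the PASAT as defined by established normative data using ≥1.5 standard deviations below the mean (36").

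**Sample.** "we will recruit a sample of 20 individuals with MS who meet the inclusion criteria", so that "we have 15 individuals in the final sample (allowing for 25% attrition"). All are treated, in three groups scheduled at different times of day. There is no comparator.

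**Timing of the PASAT.** A research assistant will "perform participant screening on the inclusion criteria, the Get Active Questionnaire and the PASAT" in the MS clinics. Those found eligible then attend a baseline session of about 120 minutes with the Table 3 measures, and Table 3 lists the PASAT. Follow-up takes place within two weeks of the last session, with alternate forms where these are possible.

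**Outcome and analysis.** In Stage 4, "The secondary outcome measure is CF performance on the PASAT", and "CF scores will be derived according to previously documented procedures (36"). This is the same reference that supplies the eligibility norms. "Comparisons between baseline and follow-up on the outcome measures for all completers will be conducted using" t-tests.

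**Decision rule.** "The intervention will be considered effective if at least a small effect size (i.e., improvement in CF) is observed between baseline and follow-up". Stage 5 then ties the planned RCT to the CF findings.

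**The concern.** The variable that selects participants is also the variable on which the intervention is judged, in one arm with no control. Three things other than the intervention can produce a small observed gain: sampling noise in about 15 people, practice on a repeated test, and regression to the mean if the score that triggered selection is also the starting point. The Stage 4 rule allows for none of them and turns any such gain into a statement that the intervention works.

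At stake are the efficacy conclusion a reader would take from the report and the effect size carried into RCT planning. How much regression to the mean contributes depends on one fact that the article does not fix: whether baseline is the screening PASAT or a new one.

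**Working it through.** **The plan's own figure.** 15 / (1 − 0.25) = 20, so the enrolment number reproduces. The protocol gives no power or error-rate calculation for the effectiveness rule.

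**Inputs.** From the protocol: n = 15 completers, a cut 1.5 SD below the normative mean, one arm. Assumed, because the protocol gives no values: small means d ≥ 0.2, with d = mean change / SD of change; retest correlation r as shown; normal scores with SD 1; true intervention effect zero throughout.

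**Step 1: chance alone.** The observed d reaches 0.2 when t ≥ 0.2 × √15 = 0.775 on 14 degrees of freedom. P = 22.6%. For 12 completers it is 25.1%, and for 20 it is 19.1%. This is the reference level for everything below.

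**Step 2: fresh PASAT at baseline, screening equally correlated with baseline and follow-up.** The expected screening-related regression is the same at both later tests, so it cancels in their difference. The rule is met about 22% to 23% of the time, the same as chance.

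**Step 3: fresh baseline plus a practice gain g.** Expected d = g / √(2(1 − r)). Chance that the rule is met, for n = 15:

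| g (SD, assumed) | r = 0.5 | r = 0.7 | r = 0.9 |
|---|---|---|---|
| 0.1 | 36% | 40% | 54% |
| 0.2 | 51% | 60% | 84% |
| 0.3 | 66% | 77% | 96% |

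These figures show sensitivity only. The protocol does not establish that any practice gain exists.

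**Step 4: fresh baseline, but screening more correlated with baseline than with the later follow-up.** Some regression then remains. Suppose about half of patients fall below the cut, so that the cut sits at the patient median and the selected group's mean lies λ = 0.798 SD below the patient mean. Correlations of 0.8 (screening to baseline) and 0.7 (screening to follow-up) leave a mean change of (0.8 − 0.7) × 0.798 = 0.08 SD. With a baseline-to-follow-up correlation of 0.7, expected d is about 0.10 and the rule is met about 36% of the time. With 0.8 and 0.6 (baseline to follow-up 0.6), expected d is about 0.18 and the rule is met about 48% of the time.

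**Step 5: screening PASAT reused as baseline.** Mean change = (1 − r)λ. SD of change = √((1 − r)² × V + 1 − r²), where V is the variance in the selected group. With the cut at the patient median, λ = 0.798 and V = 0.363. For r = 0.8: mean change 0.2 × 0.798 = 0.160; SD √(0.04 × 0.363 + 0.36) = 0.612; d = 0.26. P comes from the noncentral t with 14 degrees of freedom.

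| r (assumed) | Mean change (SD) | Spurious d | P(rule met) |
|---|---|---|---|
| 0.6 | 0.32 | 0.38 | 76% |
| 0.7 | 0.24 | 0.33 | 69% |
| 0.8 | 0.16 | 0.26 | 60% |
| 0.9 | 0.08 | 0.18 | 48% |

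Each P includes the sampling noise from Step 1.

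**The case against.** **Baseline is probably a new PASAT.** Stage 3 describes screening in clinic and then a separate session for those found eligible, and Table 3 includes the PASAT. This is the plain reading, and under Step 2 it removes most of the regression to the mean. The point stands: the 48% to 76% range is conditional and is not the expected result. What remains is that no sentence names the baseline score.

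**Table 4 does not show a single PASAT.** A reader might infer from its one pre-intervention column that screening and baseline share one administration. Its columns are phases, not visits, and that same column also holds therapist training, recruitment and consent. It does not contradict Stage 3.

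**Half below the cut is not a protocol statement.** The Introduction says that about 1 in 2 met defined criteria for CF in two studies, and the Discussion says that about half of people with MS are affected. Neither ties this to the 1.5 SD cut or to this clinic, so it is an assumption in Steps 4 and 5. A more alarming version applies the cut to a norm-like distribution, with about 7% below it. That gives a spurious d of 0.44 to 0.95 and a chance of 83% to over 99% for r = 0.9 to 0.6. It fits poorly with the prevalence the protocol reports, and it also needs the screening score to be reused. The documents do not support it as the size of the problem.

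**Practice may be small.** Alternate forms are planned where possible, the screening test already provides one exposure, and CF is a decline within the task, so a uniform gain need not change it. The Introduction also reports stable CF early in the disease course. This makes a large gain uncertain without excluding one, and group stability says nothing about regression in a selected group.

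**This is a pilot with feasibility primary.** A single arm is acceptable, and the stated aim is preliminary efficacy. The abstract has feasibility outcomes deciding whether an RCT follows, although it also names improvement in CF as the primary outcome. Nowhere is the raw pre-post d named as the RCT planning effect. This lowers the severity but does not rescue a rule that says effective.

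**Conclusion.** The concern holds as a fault in the Stage 4 decision rule, together with an unnamed baseline score. With no true effect and no bias, the rule is met about 23% of the time at n = 15, taking small as d ≥ 0.2. Any practice gain, or a closer link of screening to baseline than to follow-up, raises that by an amount the documents do not allow one to fix. Only if the screening PASAT were the baseline would regression to the mean bring it to about 48% to 76%, given r of 0.9 to 0.6 and about half of patients below the cut, both assumed.

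A reader might infer that regression to the mean is bound to make the intervention look effective. The documents do not support that, because Stage 3 more naturally describes a fresh baseline test after selection. Nor is the lack of a control arm itself the fault. Severity: should be fixed.

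**What to change.** 1. **Stage 3:** state that the screening PASAT is used for eligibility only and that the baseline-session PASAT is the sole pre-treatment value.
2. **Stage 4:** remove the statement that the intervention will be considered effective. Report the baseline-to-follow-up change in PASAT CF with its 95% CI, described as a preliminary, uncontrolled signal that is not evidence of efficacy.
3. **Stage 5:** state that the raw pre-post d will not be used as the planning effect for the RCT.

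The screening-to-baseline change may be reported descriptively, but it must not be subtracted as no-treatment drift. It contains the selection regression, which baseline-to-follow-up change largely lacks, and it covers a different interval. At r = 0.8, subtracting it would make a zero effect look like a worsening of 0.2 × 0.798 = 0.16 SD with the cut at the patient median, or 0.2 × 1.939 = 0.39 SD if the cut acted on a norm-like distribution.

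Cost: a few sentences. Stage 3 already describes PASAT screening and a baseline session whose measures include the PASAT, so no visit or participant is added. The downside is a less favourable-looking conclusion.

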### Stage 4: Analysis and dissemination

Stage 4 involves *analysis and dissemination of results*. Data will first be compiled and analyzed using IBM SPSS Statistics (version 28). Descriptive statistics will be compiled to characterize the sample. Comparisons between baseline and follow-up on the outcome measures for all completers will be conducted using *t*-tests. The primary outcome measure is feasibility and will be evaluated according to the following: eligible participants excluded or not agreeing to participate, completion rate of assessments, attendance at intervention sessions, adherence to homework, attrition, and facilitator SOAP notes. The secondary outcome measure is CF performance on the PASAT. CF scores will be derived according to previously documented procedures (36). The intervention will be considered effective if at least a small effect size (i.e., improvement in CF) is observed between baseline and follow-up. Data from the structured interview will be analyzed quantitatively. Facilitator SOAP notes will be subjected to thematic analysis. Knowledge translation will involve traditional dissemination routes (i.e., journals, conferences) with the additional plan to disseminate this research among health care professionals by providing in-service presentations and hospital rounds. We will also seek to disseminate the findings to the lay public through community presentations, and educational materials. It is our intention to include trainees at all levels in this research to educate new health care professionals on the benefits of behavioural interventions on patient outcomes. We will also engage a Patient Advisory Committee to seek input on other possible avenues of communicating the results from this study to individuals in the MS community. We will follow CONSORT reporting guidelines for pilot feasibility trials (72).

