We anticipate several outcomes from this project. First, we expect that the modifications identified by the needs assessment will be easily implementable into the planned intervention and associated facilitator manual. During the initial development in Stage 1 the intervention will be designed with these things already in mind. It is expected that each of the areas included in the needs assessment will be indicated as disruptive and currently unaddressed by at least some individuals. We anticipate that respondents will identify several areas of unmet need, particularly as they relate to treatments for fatigue, mood, and cognitive challenges. Our own group has identified a significant gap between the research progress in these areas and the services available to address these issues in standard clinical practice (75). While exercise interventions may be more readily available in the community at large, there continue to be environmental barriers to accessibility (76–78). The current intervention will be designed to address each of these components (i.e., body, mood, mind, context), highlighting once again, the flexibility of such an intervention. Second, we anticipate that at least 75% of the individuals enrolled in the intervention will complete 6/8 sessions (i.e., be successful completers). While attrition is anticipated in any intervention study, past studies have demonstrated that having at least 12 completers is sufficient to yield the necessary outcomes in a pilot study (68). Third, we anticipate that those completing the intervention will demonstrate an improvement in CF as measured by a positive and statistically significant change documented from baseline assessments. Fourth, taken together, the needs assessment and intervention are expected to inform the development of a future definitive RCT. If such an RCT were to be successful, then further RCTs to compare the efficacy of the behavioural intervention to procedural interventions (i.e., tDCS) and pharmacological interventions could be pursued.

The ultimate goal of this multi-staged project is to ensure that those with MS have access to effective interventions in real-world settings to improve the quality of their lives and enhance their ability to participate in cognitively demanding activities that they enjoy.

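### The baseline to follow-up comparisons are limited to people who attended at least 6 of 8 sessions, which leaves out low attenders who return and is likely, though not certain, to overstate improvement in cognitive fatigability

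*Protocol article*

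**What the plan says.** The analysis set is fixed in Stage 4 (Analysis and dissemination): "Comparisons between baseline and follow-up on the outcome measures for all completers will be conducted using" *t*-tests. Stage 3 (Implementation of intervention) defines the term by attendance: "Completers will be defined as individuals who attend at least 6/8 sessions (i.e., 75" per cent).

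The follow-up visit carries no such limit. Stage 3 says: "Within 2 weeks of the last videoconference session, participants will return to the Ottawa Hospital for a follow-up assessment session". Stage 4 also lists low attendance and loss to follow-up as separate feasibility items: "completion rate of assessments, attendance at intervention sessions, adherence to homework, attrition, and facilitator SOAP notes".

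On numbers, Stage 3 says "we will recruit a sample of 20 individuals with MS who meet the inclusion criteria", so that "we have 15 individuals in the final sample (allowing for 25% attrition"). The Discussion adds: "we anticipate that at least 75% of the individuals enrolled in the intervention will complete 6/8 sessions".

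Stage 4 calls the intervention effective if CF shows at least a small effect size between baseline and follow-up, without giving a number for small. Stage 5 bases the planning of the future RCT on the CF findings. The article states no comparison of all participants with follow-up data.

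**The concern.** Here a completer is someone who came to enough sessions, which is a different thing from someone with a follow-up assessment. A person who attended five sessions and came back for the visit has a baseline and a follow-up score, and the stated analysis leaves both out.

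Attendance is observed after baseline and may be related to the outcome. The article itself names mood and sleep quality as contributors to CF, and both could plausibly affect whether someone attends. If those who attend less also change less, the completer mean is too favourable. The study has no control arm that could reveal this.

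Two decisions rest on the result: the verdict on effectiveness in Stage 4 and the planning of the RCT in Stage 5. An RCT has to plan for everyone offered the programme. A completer estimate describes only those who stayed with it.

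**Working it through.** **1. The plan's own sample size.** 15 / (1 − 0.25) = 20, which agrees with the stated recruitment target. The Discussion's expectation gives 0.75 × 20 = 15 completers, so up to 20 − 15 = 5 enrolled participants could be left out of the comparisons even if all 20 return.

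**2. Shift in the mean, without a distributional model.** Let π be the proportion completing and D the mean change in completers minus the mean change in non-completers. If everyone returns,

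mean(completers) − mean(all) = (1 − π) × D.

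| π | D = −0.3 SD | D = 0 | D = 0.2 SD | D = 0.5 SD | D = 0.8 SD |
|---|---|---|---|---|---|
| 0.75 | −0.075 | 0 | 0.05 | 0.125 | 0.20 |
| 0.90 | −0.03 | 0 | 0.02 | 0.05 | 0.08 |

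The sign follows D, and the documents give no value for D.

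**3. The same shift expressed through a correlation.** Assume that attendance and change are bivariate normal with correlation ρ, and that the top 75% on attendance are kept. The shift is ρ × φ(z) / 0.75, where φ(z) = 0.318 is the normal density at the quartile, so it equals ρ × 0.424:

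- ρ = 0.2: 0.085 SD
- ρ = 0.3: 0.127 SD
- ρ = 0.4: 0.169 SD
- ρ = 0: 0
- ρ = −0.3: −0.127 SD

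**4. How often the effectiveness rule is met when nothing changes on average.** Assumptions: true mean change 0, SD of change 1, N = 20 with all returning, 75% completion, and small taken as observed mean / SD of at least 0.2. Results are by simulation.

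| Analysis | Rule met |
|---|---|
| All 20 analysed | about 19% |
| Completers, ρ = 0 | about 23% |
| Completers, ρ = 0.2 | about 34% |
| Completers, ρ = 0.3 | about 40% |
| Completers, ρ = 0.4 | about 47% |
| Completers, ρ = −0.3 | about 11% |

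The step from 19% to 23% comes only from having fewer people. The rise from 23% to between 34% and 47% comes from selection.

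**5. How much the fix can remove.** With 15 completers and k of the 5 non-completers returning, and if those who return are typical of non-completers, analysing everyone with follow-up moves the mean by k / (15 + k) × D. At ρ = 0.3, D = 0.127 / 0.25 = 0.508 SD.

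- k = 5: 5/20 × 0.508 = 0.127 SD
- k = 2: 2/17 × 0.508 = 0.060 SD
- k = 0: 0

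The full bias is removed only if every non-completer returns.

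**The case against.** The case on the other side has several parts.

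- **A completer analysis can be defended as proof of concept.** The Discussion openly states its expected CF gain for those who complete, and an uncontrolled before-and-after comparison does not isolate the effect of offering the programme in either set. This is fair, and it limits what the proposed change can achieve. It does not justify leaving out paired data that the study plans to collect, or resting the effectiveness verdict on completers alone.
- **The direction is not documented.** This stands. The article has no data linking attendance to CF change, and steps 2 to 4 show that the shift can be zero or negative.
- **Few people may be affected.** Stage 3 offers abbreviated make-up sessions and groups at three times of day. These could shrink the excluded group, although Stage 3 does not say whether a make-up session counts as attendance. Non-completers who do not return have no paired data to recover.
- **CF is a secondary outcome in Stage 4**, where feasibility is primary and none of its listed items is restricted to completers. This limits the importance of the point. The abstract calls CF primary, which is a separate inconsistency.

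A stronger reading is also tempting: that the 25% allowance covers dropout only, so that low attendance is a second loss. On that reading, if 10% to 20% of 15 retained participants attended too few sessions, the analysed number would be 15 × 0.90 = 13.5 to 15 × 0.80 = 12.0. The documents do not support this. The Discussion's 75% is a share of those enrolled and means attending 6 of 8 sessions, which gives 15 of 20, the same 15 as the final sample in Stage 3. The allowance therefore appears to cover non-completion already, and even 12 would lie within the minimum of 12 to 15 that Stage 3 cites.

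**Conclusion.** The point holds as a limited criticism of a stated analysis set. The comparisons behind the effectiveness verdict and the RCT planning exclude people with paired data because of something they did after baseline, and overstated improvement is the likely, though not certain, result.

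The size of about +0.09 to +0.17 SD, with the rule met about 34% to 47% of the time against about 19%, depends wholly on the assumptions in steps 3 and 4. None of these is established by the documents: the 75% is the article's anticipated minimum completion rate, and the cut-off of 0.2 is assumed because Stage 4 gives no number. At 90% completion the shift is less than half as large for the same gap D.

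A reader might infer that the completer restriction certainly inflates the CF result or undermines the sample size. Neither follows. The matter is worth correcting because the correction is cheap, and the feasibility conclusions do not depend on it.

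**What to change.** In Stage 4, make the main baseline to follow-up comparison the paired change in all enrolled participants who have a follow-up assessment, regardless of sessions attended. In Stage 3, state that non-completers are invited to the follow-up visit. Keep the analysis of those attending at least 6 of 8 sessions as a labelled supplementary analysis.

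The cost is a change of wording, since the visit is already planned. The estimated effect may look smaller. Selection through people who never return will remain and should be acknowledged when the result is used to plan the RCT.

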## Materials and methods

We will apply for study approval through the Ottawa Health Sciences Network Research Ethics Board.

This is a pilot study that addresses questions of *feasibility* (i.e., whether something can be done, should we proceed with it, and if so, how), as well as a specific design feature where we test the *efficacy* of the intervention on a smaller scale in preparation for a future RCT (62). This project will proceed in five stages.

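### Stage 4 would call the intervention effective on an observed small pre-post effect alone, a rule that one uncontrolled group of 12 to 15 completers can meet by chance

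*Protocol article*

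**What the plan says.** Stage 4: Analysis and dissemination makes feasibility the primary outcome and then says "The secondary outcome measure is CF performance on the PASAT". On the analysis it says "Comparisons between baseline and follow-up on the outcome measures for all completers will be conducted using" t-tests. The criterion for success follows: "The intervention will be considered effective if at least a small effect size (i.e., improvement in CF) is observed between baseline and follow-up". No significance level, confidence limit or comparator is attached to it, and small has no number and no scale.

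On size, Stage 3 says "we will recruit a sample of 20 individuals with MS who meet the inclusion criteria", so that 15 remain after 25% attrition. The Discussion adds that "having at least 12 completers is sufficient to yield the necessary outcomes in a pilot study". A completer is someone who attends at least 6 of the 8 sessions.

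The article describes its efficacy aim in several ways. Materials and methods says "we test the *efficacy* of the intervention on a smaller scale in preparation for a future RCT (62". The Introduction speaks of preliminary efficacy, and Stage 5 leaves the definitive evaluation to a later RCT. The Abstract names improvement in CF as primary, whereas Stage 4 makes it secondary. The Discussion expects completers to show a change in CF that is positive and statistically significant.

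**The concern.** The rule turns a point estimate into a verdict. With about 15 people, the observed standardised change varies widely around its true value, so a small positive estimate is a common result even when nothing has changed. The rule does not ask whether the data exclude zero.

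There is also no control group. A pre-post change on the PASAT contains whatever expectation, the passage of time and possibly repeat testing contribute. If any of these is positive, the rule is met more often, and the design cannot attribute the change to the intervention.

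At stake is a published statement that the intervention is effective. Stage 4 plans to take the results to clinicians and the lay public, and Stage 5 refers to the CF findings when planning the RCT.

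**Working it through.** **Inputs.** From Stage 3: 20 recruited, 15 in the final sample, 25% attrition. From the Discussion: 12 completers accepted as sufficient. From Stage 4: one group, baseline versus follow-up, completers only. Assumption: small means d = 0.2, where d is the mean change divided by the SD of change. The article does not say this, so a second scale is tried in step 3.

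**1. The plan's own figure.** 15 / (1 - 0.25) = 20. The recruitment target reproduces exactly. No error rate is stated for the effectiveness rule.

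**2. How often the rule is met with no true change.** The observed d equals t / sqrt(n), so the probability is P(t with n - 1 df >= 0.2 x sqrt(n)).

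| n | 0.2 x sqrt(n) | Probability |
|---|---|---|
| 12 | 0.693 | 25.1% |
| 15 | 0.775 | 22.6% |
| 20 | 0.894 | 19.1% |

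With Hedges' small-sample correction the probabilities are 23.6%, 21.3% and 18.2%.

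**3. The other scale.** Suppose small means 0.2 baseline SDs. With equal variances and pre-post correlation r, the SD of change is the baseline SD x sqrt(2(1 - r)). The threshold on the SD of change is then 0.2 / sqrt(2(1 - r)). The probabilities at n = 15 with no true change come from a simulation of 100,000 trials per setting.

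| r | Threshold on SD of change | Probability |
|---|---|---|
| 0.3 | 0.17 | 26% |
| 0.5 | 0.20 | 23% |
| 0.7 | 0.26 | 17% |
| 0.8 | 0.32 | 12% |
| 0.9 | 0.45 | 5% |

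The chance of a false verdict therefore depends heavily on a scale and a correlation that the article does not give.

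**4. What a result at the threshold means.** For an observed d of 0.2 at n = 15, t = 0.775 on 14 df and two-sided p = 0.45. Inverting the non-central t gives a 95% CI for d of about -0.31 to 0.71.

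**5. Non-specific gain.** If the intervention does nothing but scores rise by g SDs of change for other reasons, the probability at n = 15 comes from the non-central t with non-centrality g x sqrt(15). It is 36% for g = 0.1, 51% for g = 0.2 and 65% for g = 0.3. These gains are illustrations; the article gives no basis for any of them.

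**6. The standard in the Discussion.** Two-sided p < 0.05 (an assumed level; none is stated) needs an observed d of at least t(0.975, n - 1) / sqrt(n). At n = 15 this is 2.145 / 3.873 = 0.55. It is 0.64 at n = 12 and 0.47 at n = 20. At n = 15 it is 0.55 / 0.2 = 2.8 times the Stage 4 threshold under the assumption above.

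**The case against.** The strongest defence is that this is a pilot and says so. Stage 4 makes feasibility primary and commits to the CONSORT guidance for pilot feasibility trials. The Abstract says that feasibility outcomes determine whether an RCT is pursued. The t-tests will also put a significance result beside the effect size. This stands as a limit on the harm. It does not rescue the sentence, because an uncontrolled pilot is the setting that least supports a verdict of effectiveness.

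A reader might infer that the rule decides whether the RCT goes ahead. The documents do not support that. Stage 5 mentions the CF findings in planning the RCT, and the Abstract calls CF primary, so CF has some influence, but nowhere is the effectiveness verdict made the gate.

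A reader might also quote a flat false-positive rate of one in four. That needs both 0.2 on the SD of change and 12 completers. At the planned 15 it is about 23%, and it can be far lower on the baseline SD.

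The practice concern is weaker than it looks. The Introduction defines CF as failure to sustain performance within a task, so a uniform rise in PASAT score need not change it. It also reports that CF is stable over time early in the disease, and Stage 3 plans alternate forms where it can. These points lessen the practice concern but leave expectation and time effects, and they do not touch the chance rate in step 2.

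Selection on a low PASAT score raises the thought of regression to the mean. That bites hardest if the screening score also serves as baseline, which the article leaves unclear, so this point does not rely on it.

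Finally, naming the standardiser is a detail that an article may leave to a fuller document. Its absence is not the fault here; it is why the rate has to be given as a range.

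**Conclusion.** The concern holds as a fault in a stated decision rule. Applied as written, Stage 4 would label the intervention effective with no true change in about 23% of trials at 15 completers (25% at 12, 19% at 20) if small is 0.2 on the SD of change. On the baseline SD the rate at 15 is about 5% to 26% for correlations of 0.9 to 0.3. Both the number and the scale are assumptions. Any non-specific improvement raises the rate, by an amount that the documents do not let one fix. Separately, Stage 4 and the Discussion set different standards for CF. The Discussion's is worded as an expectation, so it does not repair the Stage 4 rule.

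The reach is limited to one outcome, secondary in the methods though primary in the Abstract, and to the CF signal carried into RCT planning. The feasibility conclusions are not affected.

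**What to change.** Delete the sentence in Stage 4 that declares the intervention effective. Replace it with wording such as: Change in PASAT CF will be reported as the mean paired change with a 95% CI and as a standardised mean change (standardiser: SD of change). It is a preliminary signal, and no conclusion on effectiveness will be drawn from this uncontrolled study.

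Reword the Discussion's expectation of a statistically significant change to match.

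Do not substitute a loose confidence-bound threshold. A one-sided 80% lower limit above zero would need an observed d of about 0.22 at n = 15. By construction it would be met in 20% of trials with no change, hardly better than the 22.6% now, and it would do nothing about non-specific gain.

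The change is to wording only and needs no extra participants, visits or measurements. The cost is a more modest claim.
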